### Questionnaires

***Gut irritation questionnaire.*** This questionnaire
^34^ is designed to be self-administered but subjects will be given the opportunity to ask questions about how to fill out the questionnaire. This questionnaire is slightly modified from a validated questionnaire designed to address symptoms of gastrointestinal (GI) irritation after FeSO
_4_ supplementation
^34^. It will be completed at screening, baseline (week 0) and post-intervention study visits. Subjects will be given a copy of the questionnaire to take home. Subjects will be administered this questionnaire during weekly phone calls in which they will use to copy of the questionnaire to follow along with questions as they are asked over the telephone.

***Dietary assessment.*** Study subjects will receive a Food Amount Booklet and information about the 24-hour recalls at the baseline visit (Day 0). Three separate 24-hour recalls will be collected by phone during the 4-week study. Dietary intake data will be analyzed using Nutrition Data System for Research (NDSR) software version 2016, developed by the Nutrition Coordinating Center (NCC), University of Minnesota, Minneapolis, MN. Recalls will be collected using the multiple-pass 24-h recall method, assisted by the NDSR software and the goal for each participant will be to collect two weekdays and one weekend day of intake. Outcome data from NDSR will include daily estimated energy and nutrient intake, as well as food, food group, and dietary supplement data.

### Data capture and management

The research data for this clinical trial will mainly consist of questionnaires and clinical measures in whole blood, serum, plasma and stool related to the proposed interventions. These data will be captured and managed using a REDCap database designed specifically for this study using the HNRCA’s deployment of REDCap which are both HIPAA and 21CFR11 compliant. Any data imported into the REDCap database will undergo external validation checks to ensure that the data have been imported correctly. Additionally, metadata files and data dictionaries/codebooks will be used to provide all information necessary to properly use and understand the data files. The HNRCA data management program records and stores subject identifiers separately from clinical information and results of study analyses. A study code number will identify each laboratory specimen and the master list which links the identity of the subject with the laboratory specimens will be kept in a locked file cabinet in the office of the PI and on a password-protected database on a secure Tufts server. The study team will design a tracking and data management system that will include features to improve data quality such as double data entry and edit resolution to ensure that the study variables accurately represent data on the study data collection forms. There will be a tracking and data-management system, trouble shooting for any data entry problems, an audit trail of database editing and range checks for cleaning, daily backup, cleaning of transitional databases, and transfer of master databases to SAS or SPSS for analysis by the study statistician.

### Data access

Access to the study database will be restricted to only the forms relevant for each investigator until completion of the study and the unblinding of the investigators. Additionally, protected health information will automatically be de-identified for all viewing and data exports. The data analyst will be responsible for managing the user access groups and masking all non-relevant information from the investigators.

### Audit trail and backups

A complete audit history for all data and data collection forms will be maintained using the REDCap audit feature, which records every action performed by each user while in REDCap. The study database will be subject to daily backups to tape array and daily, weekly and monthly backup copies will be maintained by Scientific Computing at the HNRCA. After key points in data acquisition, clean up and analysis, additional an additional off-site copy of the data will be created and stored within an electronic laboratory notebook using the LabArchives electronic laboratory notebook software. 

Malaria infectivity: Data will be evaluated using the 3D7 sialic acid independent strains of
*P. falciparum.* Mean infectivity of erythrocytes will be calculated from experiments performed in duplicate. Four-week change will be quantified for each subject using the logarithm of the ratio of percent parasitized erythrocytes at baseline and post-intervention. Planned comparisons will be tested using two-sample t-tests. Random effects regression will be used to incorporate day-to-day variation and test for batch effects.2) 
Bacterial proliferation potential: Bacterial proliferation potential will be evaluated using polynomial growth curve models
^23^; 18-hour growth curves will be fit from mean optical density over three replicates for each subject’s baseline and post-intervention sample. Positive and negative control values on each plate will be used to standardize values to account for day-to-day variation and utilization of different plate readers. Statistical testing will be based on planned comparisons for doubling time during the exponential phase of growth and the maximum level of growth as measured by optical density, calculated from the fitted growth curves. Two-sample t-tests will be used for pairwise group comparisons. We will adjust for multiple tests across the five selected species, using 0.05/5=0.01 type I significance level.3) 
Fecal calprotectin: Four-week change in fecal calprotectin will be performed for planned comparisons using two-sample t-tests with log transformation to satisfy normality assumptions.4) 
Iron status parameters, redox Stress, gut and systemic inflammation, gut irritation: Changes in continuous-valued clinical and biochemical outcomes will be evaluated using two-sample t-tests. Variable transformations will be used for skewed outcomes, such as number of GI symptoms.5) 
Gut microbiome: Diversity measures will be used to compare overall microbiome changes between treatment groups and testing using PERMANOVA. Functional and taxonomic profiling will be used to describe differences between treatment groups. Two-sample tests will be used to test differences in OTU relative abundances and functional predictions, with false discovery rate adjustments for testing across multiple taxa and functions. We will use clustering methods for microbiota data from gut microbiome samples to characterize the association of iron agent and presence of OTU types.

***Bias, confounding, effect modulators.*** Due to the completely randomized design, there will be protection of bias in treatment effects from known and unknown confounding variables. We will also compare subject characteristics across treatment groups and adjust for confounding effects for any variables not balanced through randomization. We are unaware of effect modulators of iron supplementation on
*P. falciparum* infectivity and bacterial proliferation. However, outcomes will be evaluated separately at different covariate levels to look for possible modulating effects to be included as interaction terms in our models. Potential effect modulators for fecal calprotectin include age and sex
^35^, and we plan to include them in the models for this outcome.

***Power calculations and sample size.*** The sample size of Phase I and Phase II was determined based on power calculations for each primary outcome as follows:

1) 
Malaria infectivity: The sample size is based on standard deviation estimates from the
*in vitro* assay of malaria infectivity by Clark
*et al.* (2014)
^36^. We pooled the estimated variability of percent increase of
*P. falciparum* growth analyzed in Clark
*et al.* (2014). Using an independent two-sample t-test, an estimated standard deviation 0.202, with a type I error of 0.05, we have at least 90% power to detect a 20% reduction in
*P. falciparum* growth using a minimum of 25 subjects per group. 2) 
Bacterial proliferation potential: Bacterial proliferation potential due to oral iron supplementation was previously studied from a similar
*ex vivo* assay
^23^. Between subject estimates of standard deviation were extracted for doubling time during the exponential phase of growth available from three species,
*S. aureus*,
*E. coli*, and
*S. Typhimurium* as 0.2470, (0.530 and 0.212), and (0.813 and 0.071), respectively, with unequal variance estimates used for
*E. coli* and
*S. Typhimurium* from pre- and post-iron supplementation. Based on two-sample t-tests with type I error at 0.01 (adjusted for planned analysis of five species), and assuming 25 subjects per group, with a minimal detectable difference of 1 hour doubling time, the power is >0.99 for all three species,
*S. aureus*,
*E. coli*, and
*S. Typhimurium*. 3) 
Fecal calprotectin: Estimates of between subject variation are from subjects with various forms of mild gastrointestinal disease
^30^. Mean fecal calprotectin was reported at 27.6 μg/g in subjects with collagenous colitis, representing mild inflammation, and at 1.9 μg/g in subjects with irritable bowel syndrome, reflecting minimal inflammation. Standard deviation in log concentration of fecal calprotectin used in the sample size calculation is 1.3 µg/g. For our study, in order to detect a 3.5 fold change in fecal calprotectin with 90% power and alpha level of 0.05, we require a minimum of 25 subjects per group. Sample size is based on two-sample t-tests with log-transformed values.

With rolling recruiting and screening, we expect enroll 10–12 subjects/month, randomly assigning them to the intervention treatment groups in blinded fashion. The relatively short length and personalized nature of the intervention will reduce the likelihood of drop outs and allow us to recruit continuously until the recruitment goals are met.

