### Study design

The Safe Iron Study is a double-blind, randomized, placebo-controlled study with iron supplementation in iron-replete older adults. For Phase I, adults are randomized to one of six intervention groups (
Table 1). For Phase II, adults are randomized to one of three intervention groups (
Table 2). For both phases, each arm undergoes an intervention period of 4 weeks, after which changes in parameters will be compared between baseline (week 0) and post-intervention (week 4) study visits.

**Table 1. T1:** Intervention groups for Phase I of the Safe Iron Study.

Subjects	Intervention Group	N	Intervention	Sampling
Fe-replete, PMW and men	Intervention 1	25	Placebo	0 and 4 weeks of intervention
	Intervention 2	25	FeSO _4_ (60 mg Fe/day)	0 and 4 weeks of intervention
	Intervention 3	25	FeSO _4_ (420 mg Fe/week)	0 and 4 weeks of intervention
	Intervention 4	25	FeSO _4_ (60 mg Fe/day) + MNP	0 and 4 weeks of intervention
	Intervention 5	25	IHAT (60 mg Fe/day)	0 and 4 weeks of intervention
	Intervention 6	25	Aspiron (60 mg Fe/day)	0 and 4 weeks of intervention

PMW, post-menopausal; FeSO
_4_, ferrous sulfate; MNP, multiple micronutrient powder; IHAT, iron hydroxide adipate tartrate

**Table 2. T2:** Intervention groups for Phase II of the Safe Iron Study.

Subjects	Intervention Group	N	Intervention	Sampling
Fe-replete, PMW and men	Intervention 1	25	FeSO _4_ (120 mg Fe/d)	0 and 4 weeks of intervention
	Intervention 2	25	IHAT (120 mg Fe/d)	0 and 4 weeks of intervention
	Intervention 3	25	Aspiron (120 mg Fe/d)	0 and 4 weeks of intervention

PMW, post-menopausal; FeSO
_4_, ferrous sulfate; IHAT, iron hydroxide adipate tartrate

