### Study timeline and visits

Illustrated in
Figure 1 (Phase I) and
Figure 2 (Phase II), eligible subjects will be identified using pre-screening and screening procedures, as described above. Once an eligible subject is identified and wishes to participate, they will complete an enrollment visit for which informed consent (Supplementary File 2, available as
*Extended data*
^21^) is obtained and instructions for stool sample collection are reviewed. The eligible subject is then randomized to a treatment group. The subject returns for a baseline, pre-intervention visit (week 0) for which a stool sample, fasted blood sample and questionnaire assessing signs and symptoms of gastrointestinal health (Gut Irritation Questionnaire) are collected, followed by standard continental breakfast (English muffin or bagel, spreads, coffee, juice and fruit). Oranges (juice, marmalade, or fresh fruit), and teas will not be offered, as those foods decrease the absorption of iron in the body. Immediately following breakfast, subjects will be administered the assigned intervention agent. After 2 hours, a post-prandial, post-dose, blood sample is collected. Instructions for intervention agents are reviewed with the subjects and they are dispended study supplements sufficient for 4 weeks. During the 4-week intervention period, subjects complete weekly Gut Irritation Questionnaires in addition to three 24-hour dietary recalls via telephone. After the 4-week intervention, subjects return for a post-intervention visit which follows the same procedures as the baseline visit.

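### The stated arm comparison of GI symptoms, read as a week-0 to week-4 change, leaves out the interim weekly reports and cannot detect a difference that resolves before week 4

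*Protocol article*

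**What the plan says.** All references are to the Protocol article.

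- **Collection.** Study timeline and visits: "During the 4-week intervention period, subjects complete weekly Gut Irritation Questionnaires in addition to three 24-hour dietary recalls via telephone". The Questionnaires section gives the visit schedule, "It will be completed at screening, baseline (week 0) and post-intervention study visits", and adds the calls: "Subjects will be administered this questionnaire during weekly phone calls". Table 3 likewise marks the questionnaire at screening, at both study visits and within the 4 weeks.
- **Status.** Hypothesis and objectives lists gut irritation among the indicators that make up the safety profile. The Outcomes text does not name the questionnaire as a primary or secondary outcome, and no sample size rests on it.
- **Analysis.** Statistical methods, item 4, covers gut irritation together with iron status, redox stress and inflammation: "Changes in continuous-valued clinical and biochemical outcomes will be evaluated using two-sample t-tests". It then adds: "Variable transformations will be used for skewed outcomes, such as number of GI symptoms". The general text of the same section also allows linear models with covariates. It mentions no repeated-measures, cumulative, peak or any-episode analysis of symptoms.
- **Time points.** Study design states the general rule for both phases: "changes in parameters will be compared between baseline (week 0) and post-intervention (week 4) study visits".
- **Other use.** Data and safety monitoring uses a GI symptom questionnaire to follow tolerance. The rationale for the study population says that subjects' health is followed weekly.

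**The concern.** Weekly questionnaires are worth collecting mainly because intolerance to oral iron may come and go within four weeks. If the arms are compared only on the week-4 report minus baseline, a group difference present in weeks 1 to 3 and gone by week 4 leaves no trace in the comparison. A difference that persists is estimated from one on-treatment report when about four exist.

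The article relies on GI tolerability in several places. The dose rationale expects few complaints with IHAT or Aspiron. The weekly-dosing rationale cites fewer GI complaints. Progression to Phase II depends on adverse effects being absent or no greater than with FeSO4. For the micronutrient-powder arm the hypothesis is that the safety profile is unaffected, so an insensitive comparison would favour it.

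**Working it through.** **1. Reports left out.** The article does not state the number of calls. Three interim calls (weeks 1 to 3) plus the week-4 visit make four on-treatment reports. A week-0 to week-4 change uses one and leaves three (75%). If a fourth call is made besides the visit, four of five (80%) are left.

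**2. The plan's own figure.** No power or sample size is given for GI symptoms. The nearest gut outcome with a calculation is fecal calprotectin: a 3.5-fold change (ln 3.5 = 1.253), SD 1.3 on the log scale, 90% power, alpha 0.05 (taken as two-sided). The normal approximation gives n = 2 × (1.960 + 1.282)² × (1.3/1.253)² ≈ 23 per group, and the exact t gives 24. The stated minimum of 25 is consistent with this, and 25 per arm is used below.

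**3. Assumptions for symptoms (not in the documents).** SD = 1 at every time point, one correlation ρ between any two reports including baseline, four on-treatment reports, and a linear model.

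**4. Variance per subject of each summary.**

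- Week-4 change: 2(1 − ρ)
- Mean of weeks 1–4 minus baseline: (1 + 3ρ)/4 + 1 − 2ρ
- Week 4 adjusted for baseline: 1 − ρ²
- Mean of weeks 1–4 adjusted for baseline: (1 + 3ρ)/4 − ρ²

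| | ρ = 0.3 | ρ = 0.5 | ρ = 0.7 |
|---|---|---|---|
| Week-4 change | 1.40 | 1.00 | 0.60 |
| Mean change | 0.875 | 0.625 | 0.375 |
| Precision ratio (change scale) | 1.6 | 1.6 | 1.6 |
| Week 4, baseline-adjusted | 0.91 | 0.75 | 0.51 |
| Mean, baseline-adjusted | 0.385 | 0.375 | 0.285 |
| Precision ratio (both adjusted) | 2.4 | 2.0 | 1.8 |

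Each ratio compares like with like, so it isolates what the weekly reports add.

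**5. Detectable difference** at 25 per arm, 80% power, two-sided 0.05: (1.960 + 0.842) × √(2 × variance/25). At ρ = 0.3/0.5/0.7 it is 0.94/0.79/0.61 SD for the week-4 change and 0.74/0.63/0.49 SD for the mean change.

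**6. Power for an assumed 0.8 SD difference** (noncentral t, 25 per arm, ρ = 0.3/0.5/0.7).

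| Pattern | Week-4 change | Mean change |
|---|---|---|
| Weeks 1–2 only | 0.05/0.05/0.05 | 0.32/0.42/0.62 |
| Sustained, weeks 1–4 | 0.65/0.79/0.95 | 0.84/0.94/0.995 |

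For the transient pattern the week-4 test has power equal to alpha. The baseline-adjusted mean has 0.61/0.62/0.74.

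**7. The opposite case.** If the difference appears only in week 4, its four-week mean is 0.8/4 = 0.2 SD. The mean change then has power 0.12/0.14/0.21 against 0.65/0.79/0.95 for the week-4 change. That is why the week-4 change should stay as a supportive analysis.

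**The case against.** **The window is inferred.** Item 4 gives no time points, whereas the items on malaria infectivity and calprotectin say that the change is over four weeks. The counting window for the number of symptoms is undefined, so a count across the weekly reports is not excluded. This stands: that GI symptoms are analysed only from week 0 to week 4 is a reading of item 4 together with Study design. But that is the natural reading, and no stated comparison uses the interim reports under any other.

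**This may be detail for the analysis plan.** The article is condensed, no analysis plan is shown, and gut irritation is not a listed primary or secondary outcome. This limits the weight of the point. It does not remove it, because the article does fix a method for gut irritation, and followed as written that method sets collected data aside.

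**The reports are used elsewhere.** A reader might infer that the weekly reports go unused in the trial and that transient intolerance would be missed altogether. The documents do not support that: the questionnaire serves tolerance monitoring, and health is followed weekly. Neither is a comparison between arms, however.

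**The gain can be overstated.** Setting an unadjusted week-4 change against a baseline-adjusted mean gives 3.6, 2.7 and 2.1 (1.40/0.385, 1.00/0.375, 0.60/0.285). Part of that comes from baseline adjustment, which the plan already allows, so it should not be credited to the weekly reports.

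**Inferences that go too far.** The documents give no figure showing that most counts are zero in healthy adults, and the plan provides transformations and graphical checks. Nor do they show that the planned test would generally find no difference: for a sustained 0.8 SD effect its power is 0.65 to 0.95 under the assumptions above.

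**Conclusion.** The point holds in limited form. The questionnaire is given weekly, the only stated between-group analysis of GI symptoms is a t-test on a possibly transformed change, and with the general rule on time points that change runs from week 0 to week 4. That comparison would not detect a difference that has resolved by week 4. This presumes that the week-4 questionnaire does not ask back over the whole period; the article gives no recall window.

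Using the weekly reports gives about 1.6 times the precision on the change scale, or 2.4/2.0/1.8 times with baseline adjustment on both sides. These figures rest on assumed equal variances, a common correlation of 0.3 to 0.7, four on-treatment reports and an effect of similar size in each week. They come from a linear model, so they illustrate the gain and do not predict it for a count model.

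No stated sample size or primary analysis changes. The change is worth making because gut irritation belongs to the safety profile and the data are already being collected.

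**What to change.** In item 4 of Statistical methods, define the gut-irritation comparison as the arm contrast averaged over weeks 1 to 4. Take it from one repeated-measures model of the weekly symptom counts, for example negative binomial, or Poisson with robust standard errors, with arm, week and baseline count as terms. State which reports count as weeks 1 to 4, including whether a call is made in week 4 besides the visit. Keep the week-4 change as a supportive analysis. The new contrast replaces the present comparison and so adds no test to the safety-profile family.

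The cost is a revised sentence and modest programming, with no new data. One small drawback is that the interim reports are taken by phone while the visit questionnaire is designed for self-completion. Mode therefore varies with week, and week must be in the model. At the time of writing Phase II screening had not begun, so the definition can be set in advance there. For Phase I it should be fixed before the allocation key is opened.

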### Hypothesis and objectives

We will robustly test our formal hypotheses yielding useful answers to the primary questions about the relative safety and efficacy of these novel forms of iron in iron-replete subjects. This study will address the major side effects of oral iron supplementation of iron-replete subjects. Specifically, we will compare the effects of two novel forms of iron and the widely used ferrous form on malaria (
*Plasmodium falciparum*) infectivity of host erythrocytes (assessed
*ex vivo*), bacterial proliferation (of selected species) in the presence of host plasma (assessed
*ex vivo*), redox stress and inflammatory stress (assessed
*in vivo*), gut irritation (assessed
*in vivo*), effects on the gut microbiome (assessed
*in vivo*). This set of indicators is referred to as the “safety profile”. Additionally, iron utilization (assessed
*in vivo*) will be compared to evaluate efficacy.

In Phase I, we will test the following research questions underpinning formal hypotheses using the design detailed below:

1. Does IHAT, a novel form of iron, produce beneficial and/or adverse effects comparable to FeSO
_4_ at equivalent iron doses?

IHAT and FeSO
_4_ administered at 60 mg Fe/day will produce comparable responses in malaria infectivity, bacterial proliferation, and iron status parameters. However, IHAT will produce less gut/systemic inflammation, and fewer effects on the microbiome.

2. Does Asprion, a novel form of iron, produce beneficial and/or adverse effects comparable to FeSO
_4_ at equivalent iron doses?

Aspiron and FeSO
_4_ administered at 60 mg Fe/day will produce comparable responses in malaria infectivity, bacterial proliferation, and iron status parameters. However, Aspiron will produce less gut/systemic inflammation, and fewer effects on the microbiome.

3. Are the adverse effects of FeSO
_4_ affected by co-administration of a multi-micronutrient powder (MNP)?

The safety profile of FeSO
_4_ for iron-replete individuals is not affected by its administration with a multiple micronutrient powder.

4. Are the beneficial and/or adverse effects of FeSO
_4 _comparable when administered daily or weekly?

The timing of FeSO
_4_ administration will not affect malaria infectivity, bacterial proliferation, and iron status parameters; however, weekly administration will produce less gut/ systemic inflammation and fewer effects on the microbiome.

In Phase II, we will test the following formal hypotheses using the design detailed below:

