1. Does IHAT, a novel form of iron, effect positive improvements in iron status comparable to FeSO
_4_ at equivalent iron doses, while producing fewer adverse effects?

IHAT and FeSO
_4 _administered at 120 mg Fe/day will produce similar increases impacting iron status in Fe-replete subjects. However, IHAT will produce relatively lower increases in
*ex vivo* malaria infectivity,
*ex vivo* bacterial proliferation, redox stress, gut/systemic inflammation, and fewer effects on the hindgut microbiome.

2. Does Aspiron, a novel form of iron, effect improvements in iron status comparable to FeSO
_4_ at equivalent iron doses while producing fewer adverse effects?

Aspiron and FeSO
_4 _administered at 120 mg Fe/day will produce similar increases on iron status in Fe-replete subjects. However, Aspiron will produce relatively lower increases in the
*ex vivo* malaria infectivity,
*ex vivo* bacterial proliferation, redox stress, gut/systemic inflammation, and fewer effects on the hindgut microbiome.

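### PERMANOVA has no sign, so it cannot by itself support the hypotheses that IHAT, Aspiron and weekly FeSO4 affect the microbiome less than daily FeSO4

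*Protocol article*

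**What the plan says.** The Phase I hypotheses (Hypothesis and objectives) include, for IHAT, "However, IHAT will produce less gut/systemic inflammation, and fewer effects on the microbiome"; for Aspiron, "However, Aspiron will produce less gut/systemic inflammation, and fewer effects on the microbiome"; and for the weekly schedule, "weekly administration will produce less gut/ systemic inflammation and fewer effects on the microbiome". In Phase II both novel forms are expected to show smaller increases in several markers, including "redox stress, gut/systemic inflammation, and fewer effects on the hindgut microbiome". The micronutrient-powder hypothesis is of another kind: the safety profile of FeSO4 "is not affected by its administration with a multiple micronutrient powder".

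Under Planned comparisons, the article says that testing is arranged to follow the hypotheses through pairwise comparisons with FeSO4. Placebo is not among the listed comparisons. Item 5 of Statistical methods gives the overall microbiome test: "Diversity measures will be used to compare overall microbiome changes between treatment groups and testing using PERMANOVA". It adds descriptive profiling and clustering, and at feature level: "Two-sample tests will be used to test differences in OTU relative abundances and functional predictions", with false discovery rate adjustment. It names no measure of how far each arm's microbiome moved.

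**The concern.** The three directional hypotheses are about the size of a disturbance. The overall test named for them asks a different question, namely whether two arms' changes differ in any way. Because the pseudo-F statistic is unsigned, a significant result fits a gentler new form, a harsher one, or one that is equally disturbing but acts on other taxa.

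The feature-level tests do not close the gap. If a taxon rises more under IHAT than under FeSO4, either IHAT raised it or FeSO4 lowered it. A list of such taxa does not add up to an amount of disturbance per arm.

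The article counts the microbiome as part of the safety profile, and a smaller microbiome effect is one of the expected advantages of the novel forms. If a significant PERMANOVA or a list of differing OTUs were read as confirming that advantage, the reading would go beyond what those analyses show.

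**Working it through.** The plan gives no microbiome sample size, effect size or power, so there is no figure of its own to reproduce. The only document inputs are 25 subjects per arm and alpha 0.05. Everything else below is assumed.

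**Why the test has no sign.** For two arms of n subjects each, N = 2n, pseudo-F = (SS_T − SS_W) / [SS_W / (N − 2)]. With Euclidean distance on subject-level change vectors, the between-arm term is SS_T − SS_W = (n/2)·‖m_new − m_Fe‖², where m is an arm's mean change. It depends only on the separation between the two mean changes, not on which is longer.

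**Setting A.** 25 per arm, 40 features, unit-SD noise in the changes, FeSO4 shift of length 2.0 spread over 10 features, 299 label permutations, 600 runs. The signed comparator is a two-sample t-test on each subject's length of change, with direction read off.

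| Effect of new form | True separation | PERMANOVA rejects | Signed test: less | Signed test: more |
|---|---|---|---|---|
| none | 2.0 | 0.990 | 0.280 | 0.000 |
| half, same taxa | 1.0 | 0.332 | 0.188 | 0.000 |
| identical | 0 | 0.052 | 0.017 | 0.025 |
| 1.5 times, same taxa | 1.0 | 0.370 | 0.002 | 0.365 |
| twice, same taxa | 2.0 | 0.977 | 0.000 | 0.972 |
| equal size, other taxa | √(4+4) = 2.83 | 1.000 | 0.030 | 0.020 |
| equal size, opposite | 4.0 | 1.000 | 0.023 | 0.035 |
| twice, other taxa | √(4+16) = 4.47 | 1.000 | 0.000 | 0.977 |

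Rows with equal separation have about equal rejection rates. For 0.332 and 0.370, the Monte Carlo standard error of the difference is √(0.332·0.668/600 + 0.370·0.630/600) = 0.028, so the gap of 0.038 is 1.4 standard errors. Half and 1.5 times cannot be told apart by this test.

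The signed test keeps its errors low but has little power here. The expected squared length of a subject's change is 40 + 4 = 44 with the FeSO4 shift and 40 without it, so noise dominates each subject's distance.

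**Setting B.** 25 per arm, 50 features, unit SD at each visit (√2 for the change), shift 2.5 along one feature, 299 permutations, 400 runs. The signed comparator is the difference in squared length of the arms' mean changes, bias-corrected by averaging cross-products between different subjects. It uses a jackknife standard error and claims fewer effects if z < −1.96.

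| Scenario | PERMANOVA rejects | Signed contrast claims fewer |
|---|---|---|
| no effect in either arm | 0.04 | 0.01 |
| FeSO4 only | 0.89 | 0.88 |
| IHAT only | 0.90 | 0.00 |
| IHAT half of FeSO4, same direction | 0.24 | 0.54 |
| equal size, same direction | 0.07 | 0.02 |
| equal size, 60 degrees apart | 0.91 | 0.01 |
| equal size, orthogonal | 1.00 | 0.03 |

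With a smaller shift of 1.5 in FeSO4 only, the signed contrast detects it in 15% of runs, against 38% for PERMANOVA.

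**Permutation unit.** With two stools per subject and no treatment effect (300 runs), permuting stools freely rejected in 42% to 85% of runs for within-subject correlations of 0.3 to 0.8. Permuting subjects' change vectors gave about 5% to 8%. The article speaks of changes, which suggests the second; the fix states it.

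**The case against.** An omnibus test followed by descriptive and feature-level results is ordinary practice, and using an undirected test for a directional hypothesis is not in itself an error. Item 5 is a short paragraph in a condensed article, and the choice of index and distance may properly sit in a fuller document. The diversity measures could include a single alpha-diversity index, whose mean change shows direction. Short-chain fatty acids also belong to the microbiome outcome and can be compared with a sign. All of this stands. However, the article is not silent: it names a test and says that testing follows the hypotheses. A single diversity index can also stay level while composition shifts.

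Four stronger readings are tempting and are not supported:

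- A reader might infer that PERMANOVA rejects whenever the disturbance is equal. It does so only when the pattern differs. With the same size and pattern it rejected in 5% to 7% of runs, and since all these arms deliver iron, a shared pattern is a natural case.
- The near-certain rejection at equal size is not a general inflation of type I error. It rests on an assumed shift in different taxa.
- Nothing in the article makes a significant PERMANOVA the sole evidence for fewer effects.
- The microbiome is not the only outcome with such a mismatch. Hypotheses of comparable or similar response are also tested by ordinary two-sample t-tests. Nor are all microbiome hypotheses directional, since the micronutrient-powder one predicts no change.

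**Conclusion.** The point holds for the three directional hypotheses (IHAT and Aspiron in both phases, weekly FeSO4 in Phase I). The overall test named in item 5 responds about equally to less and to more disturbance at the same separation, and also to equal disturbance in different taxa. No other listed analysis measures the amount of disturbance per arm. A significant PERMANOVA or OTU result therefore does not by itself support fewer effects.

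The lack of a sign follows from the form of the statistic and needs no assumption. The rejection rates are illustrative only: they depend on assumed shift sizes, patterns, feature counts and Gaussian noise. The outcome is secondary and does not enter the sample size, so this is worth correcting but does not touch the primary analyses.

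**What to change.** In item 5:

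1. Keep PERMANOVA as a test of any difference, run on subject-level changes with subjects permuted.
2. Add one pre-specified signed measure of baseline-to-week-4 disturbance. Either the bias-corrected squared length of each arm's mean change or each subject's baseline-to-week-4 distance would serve; others are possible.
3. Compare IHAT, Aspiron and weekly FeSO4 with daily FeSO4 on that measure, with an estimate and confidence interval. In Phase I, use the placebo arm to allow for background drift. Phase II has no control group, so measure from each subject's own baseline and say that drift common to the arms is included.
4. Claim fewer effects only if the interval excludes zero in the favourable direction, and state that PERMANOVA or OTU differences alone are not enough.

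The cost is wording and a short additional analysis. Stool is already collected at both visits, so no samples or subjects are added. The drawback is modest power for small differences: 15% for the squared-length contrast at the smaller shift in Setting B, and 28% for subject-level distance in Setting A even when the new form had no effect.
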